#### Secondary outcomes and safety outcomes

The differences in EQ-5D-5L utility values at 1- and 3-month follow-ups compared to baseline will be included in the secondary outcomes. Other secondary outcomes include changes in pain intensity VAS, time-intensity curve, pain map, EQ-VAS score, PSQI, PGIC, CGI-I, and satisfaction with App usage. The occurrence rate of AEs and severe AEs (SAEs) will be used as safety outcomes.

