**Discussion:**

The PreMaSy study aims to evaluate the effectiveness and safety of a novel App-based, patient-centered, self-assessment management system for chronic intractable pain. A randomized controlled trial is designed to test the non-inferiority of this precise management system compared to the monthly online follow-ups. It is also expected to yield valuable experiences regarding precision medicine.

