**Fig. 2 Fig2:**
[figure not shown]
Standard Protocol Items: Recommendations for Interventional Trials (SPIRIT) figure

Participants will then undertake the SCS electrode implantation and enter the 10-day (± 4) test period. Pain intensity will be monitored during this time. Only participants who have an improvement of no less than 50% in visual analog scale (VAS) will undertake the implantable pulse generator (IPG) implantation. After the IPG implantation, participants will be randomized (1:1) into one of the two groups: the experimental group (EG) with PreMaSy or the control group (CG) with conventional follow-ups. The randomization will be generated by computers and concealed from the recruitment team and data analysis team. The participants and their physicians, however, will not be blinded from their own randomization results, because the consequent assessments are dependent on which group they are in. The detailed assessments of the two groups are shown in Fig. 2. Participants in CG will take follow-ups only at 1, 3, and 6 months post-operative, while participants in EG will take additional monthly quality of life assessments and daily pain characteristics assessments, which can be done in a customized App. These results will be automatically monitored and timely interventional appointment will be scheduled whenever the intervention threshold is reached.

The PreMaSy study protocol was written in accordance with the Standard Protocol Items: Recommendations for Interventional Trials Statement (SPIRIT). A SPIRIT checklist is included in Additional file 1. The trial will be carried out according to the principles of the Declaration of Helsinki (Edinburgh version, 2000).

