**Fig. 3 Fig3:**
[figure not shown]
The daily assessments designed for the App. **A** Slider of VAS for general pain intensity. The current position indicates 5.0 out of 10.0. **B** Time-intensity curve for pain temporal characteristics. The *x*-axis depicts 24 h in a day in 3-h increments, and the *y*-axis depicts the pain intensity. The red curve simulates a patient’s hand-drawn curve. **C**, **D** Simplified pain map based on the dermatome pattern. There are a total of 25 pairs of body area presented, including 12 front (**C**) and 13 back (**D**). The indicators highlighted in blue simulate selections from an imaginative candidate

The monthly assessment section, on the other hand, focuses on the long-term pain-related quality of life. The Five-Level EuroQol Five-Dimensional Questionnaire (EQ-5D-5L) is a widely used instrument for assessing general health that consists of mobility, self-care, usual activities, pain/discomfort, and anxiety/depression [21]. We used the published value set for China to evaluate various health statuses [34]. The EQ-VAS is used as well for the global health condition. Sleep quality is assessed by the Pittsburgh Sleep Quality Index (PSQI) with 18 items covering seven categories [4]. Patients’ Global Impression of Change (PGIC) and Clinical Global Impressions-Improvements (CGI-I) are two seven-level questionnaires that measure the perceptions of the improvements in the participants’ overall health conditions, respectively from their own [45] and their physicians [3].

Impedance tests, parameter adjustments, adverse events (AEs), and other hardware-related issues are collected. Participants and their physicians are also asked to take satisfaction surveys based on their App usage experiences and encouraged to provide feedback. All aforementioned assessment modules will be activated automatically when the profile of a participant is established, and in order to enhance compliance, notifications of incomplete assessments will be sent at a set time.

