### Interventions

During the test period, electrode implantation and IPG implantation will be undertaken in patients who qualify. After surgery, stimulation parameters will be optimized for analgesia. In our prior work, we have described the implantation surgery, stimulation device, and programming procedure in detail [31]. The aforementioned App will be utilized for subsequent follow-ups and pain management. Upon enrollment, an App account will be assigned to each participant. They will be instructed to activate the account and fill up the profile. As soon as they undergo the implantation procedure and are randomly assigned to either EG or CG, the App will only display contents exclusively to their group.

For participants in CG, they will be scheduled for follow-ups at conventional intervals, i.e., 1, 3, and 6 months post-operative. They can only access monthly assessments during the corresponding months. For participants in EG, on the other hand, the precise management system will be implemented. In addition to the standard follow-ups, they will be asked to complete every monthly assessment throughout the 6-month follow-up period. They will have access to the daily assessments in which they will be instructed to record and track their pain characteristics. Pain intensity VAS data collected after the electrode implantation and prior to the IPG implantation will be averaged and served as the baseline. The interventional threshold will be a minimum clinically significant difference (MCSD) of 20 mm (out of 100 mm VAS) [27] added to the baseline value. The system will monitor each participant’s daily VAS score automatically. If the score surpasses the threshold three times in a row, an alarm will be sent to their physicians and a remote programming appointment will be scheduled.

To improve adherence, the background system will monitor the assessments’ completion status, and specialists will be allocated to inquire about the incompletion. Other concomitant care including medications are only permitted by approval of investigators. Both CG and EG participants have the same access to report hardware-related issues and satisfaction with App usage. In the case of adverse events (AEs) or unexpected worsening, they may also schedule an urgent appointment.

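### Adverse event rates are the safety outcome, but the experimental group has more clinical contact than the control group, so mild events may be recorded unequally.

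*Protocol article*

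**What the plan says.** Safety is a stated aim. The Discussion part of the Abstract says: "The PreMaSy study aims to evaluate the effectiveness and safety of a novel App-based, patient-centered, self-assessment management system". The outcome that serves this aim is given under Secondary outcomes and safety outcomes: "The occurrence rate of AEs and severe AEs (SAEs) will be used as safety outcomes".

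The contact schedules are fixed by arm:

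- **CG.** Trial design: "Participants in CG will take follow-ups only at 1, 3, and 6 months post-operative". Interventions adds, of the App: "They can only access monthly assessments during the corresponding months".
- **EG.** Interventions: participants are "asked to complete every monthly assessment throughout the 6-month follow-up period", on top of the standard follow-ups. They also make daily entries: "They will have access to the daily assessments in which they will be instructed to record and track their pain characteristics". Three consecutive scores above the threshold send an alarm to the physician and lead to a remote programming appointment.

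App design places the CGI-I, a physician's rating, in the monthly section. On adverse events it says: "Impedance tests, parameter adjustments, adverse events (AEs), and other hardware-related issues are collected". It does not say when or by what question they are elicited in either arm. Interventions gives both arms equal access to report hardware-related issues and lets participants book an urgent appointment for an adverse event or unexpected worsening. Trial design states that participants and physicians know the allocation.

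**The concern.** An adverse event rate counts events that occurred and were also noticed and recorded. If one arm is seen more often, its recorded rate can be higher with the same underlying risk. Here the extra contact is part of the EG strategy, so the imbalance is there by design, and neither participants nor physicians are blinded.

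Severe events should come to light in either arm. Mild or short-lived ones are the exposed group: a CG participant may have forgotten them by the next follow-up, while an EG participant may mention them at an extra monthly assessment or an alarm appointment. A reader of the results would see two rates side by side and could not separate harm from detection. An event never elicited in CG cannot be recovered at the analysis stage, so this has to be settled in data collection.

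**Working it through.** The document gives no adverse event rate and no detection rate, so there is no stated figure on this point to reproduce. Step 1 and the waiting times in step 2 follow from the stated schedules; the rest is labelled as assumption.

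**Step 1. Contacts at which an event could come to light**

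| Contact over 6 months | CG | EG | Counted as unequal? |
|---|---|---|---|
| Follow-up or monthly assessment, with physician-rated CGI-I | 3 (months 1, 3, 6) | 6 (months 1 to 6) | Yes: months 2, 4 and 5 are EG only |
| Alarm-triggered remote appointment | none | number not fixed | Yes |
| Daily entry | none | about 180 (6 × 30) | No: intensity slider, time curve and pain map only |
| Specialist inquiry about incomplete assessments | yes | yes | Partly: not limited to one arm, but EG has more assessments that can trigger it |
| Report of hardware-related issues | on demand | on demand | No |
| Urgent appointment for an adverse event | on request | on request | No |

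**Step 2. Waiting time to the next scheduled contact**

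For an event equally likely at any time in the six months, mean wait = sum of (gap² / 2) / 6.

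- CG, gaps of 1, 2 and 3 months: (1 + 4 + 9) / (2 × 6) = 14 / 12 = 1.17 months.
- EG, six gaps of 1 month: 6 / (2 × 6) = 0.50 months.

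Now assume that an event is recorded only if a scheduled contact follows within a given window. The share of event times covered is the sum of min(window, gap) / 6.

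- Window 1 month: CG (1 + 1 + 1) / 6 = 50%; EG 6 / 6 = 100%.
- Window 2 months: CG (1 + 2 + 2) / 6 = 83%; EG 100%.
- Question covering the whole period since the last common follow-up, with full recall: 100% in both.

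The last line shows why a common question with a full look-back period matters.

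**Step 3. What unequal capture would do (illustration)**

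Observed risk = true risk × capture probability. Assume the same true risk of 30% in both arms and take the stated 41 per group. The last column is an exact binomial calculation.

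| Capture CG / EG (assumed) | Observed CG | Observed EG | Difference | Chance that EG shows the higher count |
|---|---|---|---|---|
| 0.90 / 0.90 | 27.0% | 27.0% | 0 | 45% |
| 0.80 / 0.95 | 24.0% | 28.5% | 4.5 points | 63% |
| 0.60 / 0.90 | 18.0% | 27.0% | 9.0 points | 80% |
| 0.50 / 0.95 | 15.0% | 28.5% | 13.5 points | 91% |

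For the three unequal pairs and true risks from 20% to 50%, the spurious difference runs from 0.20 × (0.95 − 0.80) = 3.0 points to 0.50 × (0.95 − 0.50) = 22.5 points. That width reflects the choice of assumptions; it is not an estimate for this trial.

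**The case against.** The strongest case against is that pain monitoring is not adverse event surveillance. App design lists four separate App sections. Neither the daily nor the monthly section is described as containing an adverse event item, and adverse events are mentioned together with hardware issues, for which both arms have the same reporting access. Both arms may also book an urgent appointment. No schedule of adverse event questions is stated for either arm, and a journal article may leave that to the full protocol or case report form. A CG follow-up that asks about everything since the last one would cover all six months.

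Much of this stands, and it rules out several stronger readings that a reader might infer:

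- **That about 180 daily entries are so many extra adverse event inquiries.** They record pain only.
- **That only EG is pursued by specialists.** The text does not limit this to one arm.
- **That a formal between-arm test of adverse events is planned.** None is stated. The concern is with rates read side by side.
- **That a particular excess in EG has been shown.** Any such figure only restates assumed capture rates.

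What remains is that the three extra monthly assessments with a physician's rating and the alarm appointments are stated design features found in EG only. Shared routes that the participant must initiate do not equalise them for mild events. The limitations paragraph concedes that differing intensity of App use cannot be fully interpreted, but does not carry this over to safety.

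**Conclusion.** The point holds in a limited form. EG has six scheduled assessments against three, plus alarm-triggered physician contact, in an open-label trial whose safety outcome is a plain occurrence rate. Detection alone can therefore raise the recorded EG rate, mainly for mild or transient events and least for serious ones. The direction of this bias is against EG, though a real benefit of EG could offset it. The size cannot be fixed from the document.

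The conclusion assumes that some events come to light incidentally at contacts made for other purposes. It also rests on the schedule in Trial design and Interventions. Two other places read differently: the Abstract calls the comparator monthly online follow-ups, and Data collection and management says that all participants are taught to complete daily pain assessments after implantation. If CG were in fact followed monthly, the six-against-three part would disappear and only the alarm appointments would remain. These passages need to be reconciled.

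A reader might also infer that EG-only events should be dropped from the comparison. The document does not support that: extra reprogramming is part of the EG strategy, and removing events found there could hide real harm.

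**What to change.** 1. At the existing 1-, 3- and 6-month follow-ups, ask both arms the same adverse event question, covering the whole period since the previous common follow-up.
2. Record for each event how it was first detected: common follow-up, extra monthly assessment, alarm appointment, staff inquiry, participant report or urgent appointment.
3. Report all adverse events and SAEs by arm in full. Beside this, tabulate the events elicited at the common follow-ups, and show EG-only detections by source. Keep every EG event in the overall safety rate.
4. Reconcile the descriptions of the CG follow-up schedule and of who completes daily assessments.

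The cost is one question, one data field and one table, with no added visit. For participants already followed up, the question and the source field may have to be completed from existing records as far as these allow.

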### Statistical methods

#### Sample size

The primary comparison in this study is the difference between EG and CG in quality of life score measuring by EQ-5D-5L. The EQ-5D-5L difference is assumed to be 0.53 with a standard deviation (SD) of 0.69 based on previous studies into the effectiveness of App-based therapy for chronic pain [40]. A sample size of 82 (41 per group) is calculated by the following formula:$$n=\frac{(1+r){({Z}_{\alpha }+{Z}_{1-\beta })}^{2}{\sigma }^{2}}{r{(\left|D\right|+\Delta )}^{2}}$$

$$Z$$ is the quantile of the standard normal distribution, $$\alpha$$ is the first-class error level, $$\beta$$ is the second-class error level for the statistical test, and $$r$$ is the allocation ratio, which is 1:1 in this equal allocation trial. Here, to detect the significant difference at a significant level of 0.05 with 80% power using a two-tailed* t* test, $${Z}_{\alpha }$$ and $${Z}_{1-\beta }$$ are determined as 1.96 ($$\alpha$$ = 0.05) and 0.84 ($$\beta$$ = 0.2), respectively. $$\sigma$$ is the expected SD of the outcome, and $$\left|D\right|$$ is the expected mean difference of the two groups. The non-inferiority limit is set at 10% [10], and $$\Delta$$ is 0.053. The sample size per group is calculated with the above formula, and the given value is 22. With the assumption of a 60% “true” responding rate and a 10% possible attrition rate, the final calculation of the sample size is 41 pairs ($$N$$ = 82).

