**Methods:**

Patients with chronic intractable pain will be screened for eligibility, and 82 participants are anticipated to be enrolled in this trial. After the electrode implantation, the stimulation effectiveness will be tested. Participants with a reduction of more than 50% in the visual analog scale (VAS) will receive implantation of an implantable pulse generator and randomized (1:1) into the experimental group or control group. All participants will be asked to take online follow-ups and complete assessments using a smartphone application. Daily pain characteristic assessments and monthly quality of life questionnaires are integrated into the App, and participants will be required to complete these assessments. The daily VAS for pain intensity will be monitored and a threshold will be set based on baseline VAS score. The interventional appointment will be scheduled once the threshold is reached. The primary outcome is the health condition and quality of life assessed by the five-level EuroQol five-dimensional questionnaire (EQ-5D-5L). Utility values of EQ-5D-5L will be assessed at baseline and 1, 3, and 6 months post-operative.

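### The stated 41 per group cannot be the randomised group size if 82 are enrolled: about 25 per group would be randomised and 22 evaluable

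*Protocol article*

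**What the plan says.** The Sample size section reports the total as follows: "A sample size of 82 (41 per group) is calculated by the following formula". The formula's own result there is 22 per group. That figure is then inflated for an assumed 60% rate of true responders and 10% attrition, after which "the final calculation of the sample size is 41 pairs".

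The order of events is set out elsewhere in the article:

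- Abstract, Methods: "82 participants are anticipated to be enrolled in this trial". The electrode implantation and the stimulation test come after this.
- Trial design: "Only participants who have an improvement of no less than 50% in visual analog scale (VAS) will undertake the implantable pulse generator (IPG) implantation". Randomisation follows the pulse generator implantation. The same section explains that the enriched design moves the point of randomisation so as to take in more true responders.
- Table 2, exclusion criterion 11: patients who improve by less than 50% on the VAS, or do not tolerate stimulation in the test period, are excluded.

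The article gives no target for the number randomised.

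**The concern.** A group exists only once patients have been randomised, and by then everyone who failed the test has left. A loss at the test can enlarge the number who must start the test, but it cannot enlarge a group. The Sample size section nevertheless divides the per-group number by 0.6 and attaches a per-group label to the result.

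The 82 enrolled in the abstract and the 41 per group in the Sample size section therefore cannot both be right. Someone planning recruitment, reviewing ethics or later reading the results cannot tell how many patients are meant to be randomised. The number entering the test matters in its own right, because every one of those patients has electrodes implanted before the filter applies.

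**Working it through.** **Inputs (Sample size section).** "The EQ-5D-5L difference is assumed to be 0.53 with a standard deviation (SD) of 0.69". The margin is 0.053, which is 10% of 0.53. The error rates are set "at a significant level of 0.05 with 80% power using a two-tailed" test, so Z = 1.96 and 0.84. The allocation ratio "which is 1:1 in this equal allocation trial". The responder rate is 60% and attrition 10%.

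**1. The plan's own figures.**

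- n = 2 × (1.96 + 0.84)² × 0.69² / (0.53 + 0.053)² = 7.465 / 0.3399 = 21.96, so 22 per group. This matches the plan.
- 22 / (0.6 × 0.9) = 40.74, so 41; 2 × 41 = 82. This also matches.

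The arithmetic reproduces. What remains is which patients the 41 and the 82 count.

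**2. If 82 are enrolled before the test (the abstract).**

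- Pass the test and are randomised: 82 × 0.6 = 49.2, or 24.6 per group.
- Evaluable after attrition: 49.2 × 0.9 = 44.3, or 22.1 per group.

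The evaluable number meets the requirement of 22. The group size is about 25, not 41.

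**3. If 41 per group are randomised (the Sample size section taken literally).**

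- Needed at the start of the test: 82 / 0.6 = 136.7, so about 137.
- Evaluable: 41 × 0.9 = 36.9 per group, well above the 22 required.

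On this reading the 82 enrolled is wrong, and the 60% has been applied to patients who have already passed.

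**4. Working back from 22 evaluable per group.**

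- Randomised: 22 / 0.9 = 24.4, so 25 per group and 50 in total.
- Entering the test: 50 / 0.6 = 83.3, so about 84. The plan's 82 differs only through rounding.

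**5. Fixed enrolment of 82.** The number who pass is then random. Taking it as binomial with a true rate of 60%, the chance of at least 50 passing is about 48%.

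**6. If the pass rate is not 60%.** Evaluable per group is 82 × rate × 0.9 / 2. Power is from the noncentral t, with the plan's |D| + Δ = 0.583 and SD 0.69. It is shown at both alphas because the Sample size section uses Z = 1.96 (one-sided 0.025), while the section on primary and additional analyses tests non-inferiority at one-sided 0.05.

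| Pass rate | Evaluable per group | Power, one-sided 0.025 | Power, one-sided 0.05 |
|---|---|---|---|
| 50% | about 18 | about 70% | about 80% |
| 60% | about 22 | 78% | 87% |
| 70% | about 26 | 85% | 91% |

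At 22 per group and one-sided 0.025, the plan's normal approximation gives 80%.

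**The case against.** The strongest reply is that nothing of substance is lost. The sums are correct, and 82 enrolled leads to exactly the 22 evaluable per group that the formula asks for. On that view the text is only loosely labelled. This stands as far as power is concerned, and it limits the point to a wrong statement of group size.

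Three stronger readings are tempting, and the article does not support them.

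- A reader might infer that the trial is underpowered, or is presented as far better powered than it is. At the planned rates it reaches its own target, and the section claims 80% power. About 95% (one-sided 0.025, 37 evaluable per group) would follow only if 41 per group were randomised, and the article never claims it.
- A reader might infer that the recruitment target is open between 82 and 137. The abstract gives a single enrolment figure, 82. The 137 arises only if 41 is taken as a randomised count.
- A reader might quote the power at one-sided 0.025 alone. The stated non-inferiority test is at one-sided 0.05, where even a 50% pass rate leaves about 80%. The mismatch between the two alphas is a separate matter.

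It can also be said that the Sample size section does not define the 60%. That is fair: reading it as the test-period pass rate is an inference. It is well supported, because the Trial design section uses the same term for patients identified by the test period, but it should be marked as an inference.

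**Conclusion.** The concern holds as a mislabelled sample size and an unstated randomisation target. With 82 enrolled, a 60% pass rate and 10% attrition, the expected numbers are about 49 randomised (about 25 per group) and about 44 evaluable (22 per group). The stated group size is too large by a factor of about 41/25 = 1.6.

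This rests on two readings: that the 60% is the test-period pass rate, and that 82 counts patients before the test, as the order of events in the abstract indicates. It takes the formula and its inputs (0.53, 0.69, 0.053) as given and does not judge them. The correction leaves enrolment, evaluable numbers and planned power essentially unchanged, so it should be fixed but does not threaten the design.

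**What to change.** Delete 41 per group and 41 pairs from the Sample size section, and state three numbers in their place:

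- evaluable: 22 per group, 44 in total;
- randomised: 25 per group, 50 in total (22/0.9, rounded up, in each group);
- entering the stimulation test: about 82 to 84, at an assumed 60% pass rate, with the 60% defined there as the pass rate if that is what is meant.

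This is a change of wording and adds essentially no patients.

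Preferably, also end recruitment when 50 have been randomised instead of at a fixed 82 enrolled, given the roughly even chance of falling short. This goes beyond wording, because the number entering the test then varies with the observed pass rate: about 100 at 50% (50/0.5) and about 71 to 72 at 70% (50/0.7 = 71.4). If enrolment stays fixed at 82, the plan should say that the number randomised is an expectation. Any statement of power by pass rate should name the alpha it uses.
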